##### Disease and treatment

2.7.4.2

The following data are extracted from the children's medical records: sex, age, diagnosis, date of diagnosis, date of treatment initiation, date of relapse, possible date of death, comorbidity, treatment (e.g., treatment protocol, medical treatment), and medical care.

##### Feasibility

2.7.4.3

The feasibility of the overall intervention and each intervention component will be assessed by acceptability, attrition, adherence, and completion (10, 30). Mild, moderate, and severe adverse events are registered (31). The parents will answer an evaluation survey after the intervention. The evaluation survey will include ratings of the relevance of the different intervention components, the time of day for both the in-hospital and at-home group-based sessions, the facilities for the in-hospital group-based sessions, whether their child was challenged during the sessions, the inspirational material, and the extent to which they used this material. Furthermore, there will be space for the parents to elaborate on their ratings.

### Sample size

2.8

The following sample size calculation is based on preliminary baseline data from the RePlay study (9) of the sum of standard scores from three gross motor domains (i.e., stationary, locomotion, and object manipulation) of the PDMS-2. With a mean of 20.03 in summed gross motor standard score and a standard deviation of 7.4 (unpublished data from RePlay, *n* = 36) (9), a 25% difference between groups, an alpha level of 0.05, and a power of 80%, we need to include 68 preschool children with cancer. Based on RePlay, we assume 20% missing data of the primary outcome at the primary endpoint (10). Therefore, we aim to include 82 preschool children with cancer. Based on the deficiencies observed within two weeks of treatment initiation (baseline score of 20.03 gross motor function), we expect a 25% difference between groups to be obtainable over 9 months of intervention.

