**Methods:**

The Social and Physical Activity as Rehabilitation for preschool Kids with cancer (SPARK) intervention includes the following components: 1) Supervised group-based social and physical activity at the hospital; 2) A parent educational program, and 3) Online supervised group-based social and physical activity in the families’ homes. The group-based social and physical activity is conducted as structured active play. We will include 82 preschool children (aged 1–5 years), newly diagnosed with cancer, who will be randomly assigned on a 1:1 ratio to either group (a) or group (b). Group (a) will receive supervised group-based social and physical activity at the hospital (component 1), and group (b) will receive supervised group-based social and physical activity at the hospital, the parent education program, and online supervised group-based social and physical activity at home (component 1–3). The primary outcome is gross motor function measured using the Peabody Developmental Motor Scales, Third Edition (PDMS-3). Secondary outcomes are parents’ knowledge of physical activity and the children's general physical function. Assessments will be conducted at treatment initiation (baseline), and 6, 9 (primary endpoint), and 12 (follow-up) months after treatment initiation. Additionally, we will qualitatively explore the parents’ and children's experiences, the rehabilitation program's potential for the children's social development, and the importance of professionals in facilitating structured social and physical activities.

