##### Gross motor function

2.7.1.1

To measure gross motor function, we use the gross motor function composite of the Peabody Developmental Motor Scales, Third Edition (PDMS-3), which assesses total gross motor function in children aged 0–6 years. To assess overall gross motor function, we use the sum of the scaled scores for the three gross motor subtest: body control (56 items), body transport (63 items), and object control (39 items) (17). All items within the subtests are scored individually with a score of 0 (i.e., the child cannot or will not attempt the item, or the attempt does not show that the skill is emerging), 1 (i.e., the child's performance shows a clear resemblance to the item mastery criteria but does not fully meet the criteria), or 2 (i.e., the child performs the item according to the criteria specified for mastery) (17). The raw score for each subtest is the sum of all the item scores. The raw scores are converted to scaled scores for each subtest, which account for age differences, and the subtest scaled scores are summed to an overall scaled score. We use the summed gross motor scaled scores for comparison between the groups. The summed scaled score can also be converted to an index score of the gross motor composite.

The assessment is administered by two trained members of the project team. The test is conducted by starting with a given item in the subtest, depending on the child's age (specified in months). The items are treated singularly until the child receives a score of 2 on three consecutive items, determining the lower level. It may be necessary to revert to earlier items to achieve three consecutive scores of 2. The preceding items are given a score of 2. The test then proceeds with further items until the child receives a score of 0 on three consecutive items, determining the ceiling level. The remaining items are then given a score of 0. The test has shown acceptable psychometric properties, including Cronbach *α* = 0.88–0.96, test–retest *r* = 0.94–0.98 (17). The previous Peabody Developmental Motor Scales, Second Edition (PDMS-2) gross motor function composite (previously called subtest) has been shown to be feasible to use for preschoolers with cancer during treatment, with 80% of the children completing the full composite at 6 months post-treatment initiation (10).

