The study design includes two active intervention groups, which can be regarded as both a strength and a limitation. Because both study arms receive active interventions, the contrast between groups may be reduced. This overlap in intervention components or mechanisms of action can attenuate observed between-group differences and may lead to an underestimation of the true intervention effect. We expect the additional intervention components to be essential, particularly given that families are spending more time at home and that the intervention is tailored to this context. On the contrary, these components have not been previously tested or evaluated in a trial, and despite a small test period prior to the SPARK RCT, their feasibility remains unknown. Still, we expect the anticipated increase in gross motor function of 25% to be attainable as this responds to an increase in standard score by five “points” across all three subtests. Additionally, the design ensures that the social element of the intervention is supported, as all children in the ward can participate in the play activities at the hospital.

As the literature and evidence are still limited on physical activity interventions and initiatives specifically for preschoolers, we chose to include numerous feasibility and evaluation measures and qualitative explorations to ensure that future interventions and initiatives can be tailored to preschoolers’ and their parents’ needs. Qualitative research within a randomized controlled trial can be a strength as it provides a comprehensive understanding of the intervention from the user's perspective (45). This broadens our understanding and allows us to explore other impacts and new questions that arise.

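### The enrolment target of 82 adds 20% to 68 instead of dividing 68 by 0.8, so it does not give 80% power under the plan's own missing-data assumption

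*Protocol article*

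**What the plan says.** Section 2.8 (Sample size) builds the target in two steps.

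- **Evaluable number.** The inputs come from RePlay baseline data on the PDMS-2: "With a mean of 20.03 in summed gross motor standard score and a standard deviation of 7.4", together with "a 25% difference between groups". From these it concludes: "an alpha level of 0.05, and a power of 80%, we need to include 68 preschool children with cancer".
- **Enrolment target.** It then allows for missing outcomes: "we assume 20% missing data of the primary outcome at the primary endpoint (10). Therefore, we aim to include 82 preschool children with cancer". The calculation linking 68 to 82 is not shown.

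Two other places bear on the inputs. Section 3.2 (Strengths and limitations) confirms the size of the effect, describing it as "an increase in standard score by five “points” across all three subtests". Section 2.7.1.1 (Gross motor function) gives the only RePlay completion figure for this outcome in the article: "80% of the children completing the full composite at 6 months post-treatment initiation". The Abstract repeats 82 as the number to be included, with 1:1 allocation.

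**The concern.** The 20% is a share of the children enrolled. Section 2.8 calls it missing data at the primary endpoint, and the RePlay figure is likewise a percentage of the children in the study. To be left with 68 after losing a fifth of those enrolled, one divides by 0.8. Adding 20% to 68 answers a different question and always gives too few.

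The contradiction does not depend on how 82 was reached, because a fifth off 82 leaves fewer than 68.

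At stake is the claim that the trial has 80% power for a five-point difference. Section 3.2 itself accepts that two active arms may narrow the contrast, so the assumed effect has no evident slack to absorb a shortfall.

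**Working it through.** **Inputs**

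- Mean 20.03, SD 7.4, 25% difference, alpha 0.05, power 80%, 20% missing: section 2.8.
- 1:1 allocation: Abstract, Methods.
- Sidedness is not stated. Two-sided is assumed because it comes closest to 68; a one-sided test would need only 56.

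**Step 1: reproduce the 68**

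- Difference: 0.25 × 20.03 = 5.0075 points.
- Standardised difference: 5.0075 / 7.4 = 0.677.
- Normal formula, per arm: 2 × (1.960 + 0.842)² / 0.677² = 34.28.
- Total: 2 × 34.28 = 68.56.

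The 68 is therefore the normal-approximation figure rounded down. Rounding each arm up gives 35 per arm, 70 in total. The t-test (noncentral t) first reaches 80% at 36 per arm, 72 in total.

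**Step 2: reproduce the 82**

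- 68 × 1.2 = 81.6, rounded up to 82. This matches the plan.
- 68 / 0.8 = 85. This does not.

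The multiplication by 1.2 is inferred, since the step is not printed.

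**Step 3: what 82 delivers**

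- Expected evaluable: 82 × 0.8 = 65.6, or 32.8 per arm.
- Largest missing share that still leaves 68: 1 − 68/82 = 17.1%.

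**Step 4: power for 5.0075 points, SD 7.4, two-sided 0.05**

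| Evaluable per arm | Total | Normal | t-test |
|---|---|---|---|
| 32.8 (82 enrolled, 20% missing) | 65.6 | 78.2% | 77.0% |
| 34 (the plan's 68) | 68 | 79.7% | 78.5% |
| 35 | 70 | 80.8% | 79.7% |
| 36 | 72 | 81.9% | 80.8% |

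If each child's outcome is missing at random with probability 20%, average t-test power for 82 enrolled is 76.8%.

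**Step 5: split the shortfall**

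- Due to the inflation step: 78.5 − 77.0 = 1.5 points by the t-test, and 79.7 − 78.2 = 1.5 points by the normal formula.
- Already present in the 68: 80 − 78.5 = 1.5 points by the t-test, or 80 − 79.7 = 0.3 by the normal formula.

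**Step 6: equivalent statements**

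- Smallest difference with 80% power at 65.6 evaluable (t-test): 5.20 points, against the planned 5.01.
- Baseline-to-9-month correlation at which baseline adjustment would restore 80%: √(1 − (5.0075/5.198)²) = 0.27.
- Enrolment for 72 evaluable: 72 / 0.8 = 90.

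**The case against.** There are four arguments against giving this much weight.

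- **The loss is small beside the uncertainty in the SD.** The 7.4 comes from 36 children. Assuming normality, its 95% interval is about 6.0 to 9.7. Across that range, t-test power at 65.6 evaluable runs from about 91% down to 54%, while moving from 65.6 to 68 changes it by 1 to 2 points. This is right, and it limits the practical importance. It does not make the arithmetic correct.
- **Setting 77% against 80% mixes methods.** The plan's 68 follows the normal approximation, on which 82 gives 78.2%, and the inflation step costs only 1.5 points. This stands, and the two sources should be kept apart as in the working. The t-test figures of 72 and 90 are a stricter standard than the plan appears to use. The normal approximation also gives less than 80%, so the conclusion is the same.
- **ANCOVA may recover the power.** With baseline PDMS-3 as a covariate, an assumed correlation of 0.3 would give 80.8% and 0.5 would give 87.6% (t-test, 82 enrolled, 20% missing). This is plausible. But section 2.8 claims no such gain and gives no correlation. Section 2.9 describes the first model as having no adjustment and names baseline adjustment only for the parent knowledge test. An unstated gain cannot support a figure derived without it.
- **The 20% is openly an assumption.** The article's only RePlay figure is at 6 months and the SPARK primary endpoint is at 9 months. Nothing in the article shows that missingness at 9 months would be higher. This is worth a sentence in the plan but is not an error, and the finding does not depend on it.

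**Conclusion.** The concern holds. On the plan's own figures, 82 children with 20% missing leave 65.6 evaluable, 2.4 fewer than the 68 required. Power for the planned difference is 77.0% by the t-test or 78.2% by the normal approximation, not 80%. Half of the 3-point t-test shortfall comes from the inflation step and half from the 68 itself.

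The power figures assume a two-sided test, equal arms, the stated SD and an unadjusted comparison. The contradiction between 82, 20% and 68 needs none of these. The error is modest in size, but it lies in the enrolment target and the power claim, and nothing elsewhere in the article repairs it.

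**What to change.** Correct section 2.8 in one of these ways and show the inflation step.

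1. **Keep 82 and restate the power:** about 77% (t-test) for a 5.0-point difference with 20% missing, unadjusted comparison, two-sided 5%.
2. **Keep 82 and recalculate for an analysis adjusted for baseline PDMS-3.** State the assumed baseline-to-9-month correlation and its source. About 0.27 or more reaches 80%. Section 2.9 would then have to name baseline PDMS-3 as a covariate in the primary model.
3. **Keep the unadjusted 80% target and raise enrolment:** to 85 (86 for equal arms) to retain 68 evaluable, or to 90 for 80% by the t-test.

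In each case, state that the test is two-sided and that the 20% is carried over from RePlay completion at 6 months, if that is its source.

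The first two options cost only rewording and no extra children; the first also means a slightly less favourable power statement. The third costs 3 to 8 more children (85 − 82 = 3; 90 − 82 = 8).

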### Statistical analysis

2.9

The primary outcome [gross motor sum of scaled scores from the three subtests (i.e., body control, body transport, and object control) of the PDMS-3] will be analyzed using analysis of covariance (ANCOVA) models with the residual variance depending on the group [intervention group (a) and intervention group (b)]. To investigate whether the impact of adjusting for the differences between the two groups could result from differences in age, diagnosis, and time since diagnosis, the groups will be compared in three different models: 1) a raw model without any adjustments, 2) a model further adjusted for diagnosis, and 3) time since diagnosis. The secondary outcome of the PEDI will be analyzed using a similar model. The Multiple-Choice Assessment will be analyzed using a Linear Mixed model to investigate post-intervention knowledge between parents in intervention group (a) and intervention group (b) while adjusting for baseline scores. Secondary analyses include within-group changes pre- and post-intervention, analyzed using paired *t*-tests. An alpha level of 0.05 will be considered significant. Descriptive statistics will be used to summarize feasibility outcomes (i.e., acceptance, attrition, completion, adherence, adverse events, and the parent evaluation survey).

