##### Level of everyday function

2.7.2.1

To measure the children's level of everyday function, we use the Pediatric Evaluation of Disability Inventory (PEDI), which assesses the capability and performance of selected functional activities of children aged 6 months to 7.5 years old through three different scales: functional skills, caregiver assistance, and modifications (18, 46). In this study, the modification scale is not used. The functional skills scale is divided into three domains: self-care (73 items), mobility (59 items), and social function (65 items), with each item scored as 0 or 1. The caregiver assistance scale is divided into three domains: self-care (8 items), mobility (7 items), and social function (5 items), with each item scored 0–5. Aggregate scores are defined as the sum of each domain and are converted to normative standard scores for each domain (18). PEDI is assessed by a trained member of the project team and is conducted as a structured interview with parents. The PEDI assessment has been shown to be feasible to use with parents of preschoolers with cancer during treatment, with a 95% completion rate at 6 months post-treatment initiation (10).

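### Section 2.9 tests the primary outcome in three models, does not say which one decides superiority, and leaves their covariates unclear

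*Protocol article*

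**What the plan says.** The outcome and time point are fixed. Section 2.7.1.1 makes the summed gross motor scaled score of the PDMS-3 the comparison variable, and section 2.1 puts the primary endpoint at nine months.

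The analysis is in section 2.9 (Statistical analysis):

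- The primary outcome "will be analyzed using analysis of covariance (ANCOVA) models with the residual variance depending on the group".
- The purpose of the several models is to see whether group differences "could result from differences in age, diagnosis, and time since diagnosis".
- To that end "the groups will be compared in three different models".
- Those models are then listed, in this order and with no further definition, as "1) a raw model without any adjustments, 2) a model further adjusted for diagnosis, and 3) time since diagnosis".
- "An alpha level of 0.05 will be considered significant".

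No model is called primary, and none is called supportive or a sensitivity analysis. Section 2.5 stratifies randomization by age (below 36 months, or 36 months and over) and by three diagnostic groups. Table 1 schedules the PDMS-3 at baseline.

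**The concern.** A superiority trial needs one pre-stated result that decides its claim. Here the variable and visit are fixed, but the model is not. If one model gives p below 0.05 and another does not, the protocol contains no verdict, and the choice falls to whoever writes the report with the results in view.

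The stated purpose does not settle the matter. Asking whether a group difference comes from age or diagnosis is a question about confounding. In a randomized trial stratified on those two factors, covariates serve mainly to match the analysis to the design and to gain precision. That calls for one adjusted model fixed in advance.

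The description of the models also conflicts with itself, so calling one of the listed models primary would still not define it.

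**Working it through.** **1. What the text fixes and does not fix**

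| Element | Where it appears | What is unclear |
|---|---|---|
| Age | Purpose in 2.9; stratification factor in 2.5 | In none of the three listed models |
| Baseline PDMS-3 | Measured at T0 (Table 1) | Not stated for any primary-outcome model; stated in 2.9 for the parent knowledge test |
| Model 1 | Called an ANCOVA model | Said to have no adjustments, yet model 2 is *further* adjusted |
| Model 3 | Time since diagnosis | Could add to diagnosis or replace it |

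**2. The plan's own figure**

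Inputs from section 2.8: mean 20.03, SD 7.4, difference 25%, alpha 0.05, power 80%. Sidedness is not stated; two-sided is assumed.

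- Difference: 0.25 × 20.03 = 5.0075 points.
- n per arm = 2 × [7.4 × (1.960 + 0.842) / 5.0075]² = 34.28, or 68.6 in total, against the stated 68. Rounding up per arm gives 70. A one-sided test would need 28 per arm (56 in total), which does not match.
- Evaluable at 9 months: 82 × 0.80 = 65.6, taken as 66 (33 per arm).

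This is a two-group formula with no covariates.

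**3. How often the models disagree**

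Simulation inputs: n = 66; SD 7.4; difference 0 or 5.0075; randomization stratified by diagnosis; assumed diagnosis mix 50/20/30%; equal residual variances. The shares of variance (R²) explained by diagnosis and by time since diagnosis are assumptions, because the protocol gives none.

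| R² diagnosis / time | Model 3 read as | Disagree, real effect | Disagree, no effect | Any of three significant, no effect |
|---|---|---|---|---|
| 0.05 / 0.05 | replacing diagnosis | 6.8% | 2.5% | 5.8% |
| 0.05 / 0.05 | adding to it | 7.2% | 2.4% | 6.0% |
| 0.10 / 0.10 | replacing | 9.8% | 3.7% | 6.5% |
| 0.10 / 0.10 | adding | 9.0% | 4.1% | 6.7% |
| 0.20 / 0.20 | replacing | 14.3% | 4.4% | 6.0% |
| 0.20 / 0.20 | adding | 14.7% | 5.4% | 7.1% |
| 0.30 / 0.30 | replacing | 16.5% | 4.9% | 5.3% |
| 0.30 / 0.30 | adding | 17.9% | 7.5% | 8.4% |

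Time since diagnosis probably varies little: children are newly diagnosed, baseline falls within 14 days of treatment start, and T2 is 9 months ±14 days. Its R² is then more likely small, and the last two rows are doubtful. With time R² at 0.02 and diagnosis R² at 0.05 to 0.30, disagreement under a real effect is about 4 to 9%. With time R² between 0.02 and 0.10 it reaches about 6 to 15%. A fair overall range is 4 to 15%.

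**4. The raw model under stratified randomization**

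If diagnosis is balanced by design but left out of the model, the standard error is too large by a factor of about 1/√(1 − R²). The actual type I error is then 2 × [1 − Φ(1.96/√(1 − R²))]:

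- R² 0.05: 1.96/√0.95 = 2.011, giving 4.4%.
- R² 0.30: 1.96/√0.70 = 2.343, giving 1.9%.

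The raw model is conservative, which is one reason it can disagree with the others.

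**5. What baseline adjustment is worth**

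Power ≈ Φ(difference/SE − 1.96), with 33 per arm:

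- No covariates: SE = 7.4 × √(2/33) = 1.822; 5.0075/1.822 = 2.749; power 78%.
- Baseline included, assumed correlation 0.6: SE = 1.822 × √(1 − 0.36) = 1.457; 5.0075/1.457 = 3.436; power 93%.

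Simulations that also varied the strength of diagnosis and time since diagnosis gave about 76 to 82% without baseline and 92 to 98% with it. An unadjusted and a baseline-adjusted analysis disagreed in about 12 to 20% of trials with a real effect, at assumed correlations of 0.5 to 0.7.

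**The case against.** **There is an implied hierarchy.** The models run from raw to further adjusted, their purpose is to examine the impact of adjustment, and the sample size formula has no covariates. One can read this as a raw reference analysis with robustness checks. That is a fair reading, and the protocol never says the three rank equally. But it ranks none of them either, and an inferred order is not a decision rule. If the raw model was intended, it is the one that ignores the stratification.

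**ANCOVA may be taken to include baseline.** It often does. But the first model is described as having no adjustments, and the same section states baseline adjustment explicitly for a different outcome.

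**Age is already in the score.** Scaled scores do account for age, which weakens the case for age as a prognostic covariate. It remains a stratification factor, and the protocol's own purpose names it.

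**The analysis plan may settle this.** It may. But the article goes beyond leaving detail out: it lists the models in terms that conflict, and any later plan would have to correct them.

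**Stronger readings that do not hold.** A reader might infer serious type I inflation. Three independent tests would give 1 − 0.95³ = 14.3%, but these models share the same outcome data, so the figure is about 5 to 7%. A reader might also extend the point to PEDI, multiplying its six domain scores by three models to get 18 tests. The text does not support that: "The secondary outcome of the PEDI will be analyzed using a similar model" is singular, PEDI is secondary and cannot decide superiority on the PDMS-3, and multiplicity among secondary outcomes is commonly left to the analysis plan. The 26% chance of a false positive across six scores also requires independence.

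**Conclusion.** The point holds for the primary outcome alone. Section 2.9 does not say which of its three models decides superiority, and it leaves their covariates inconsistent or undefined.

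The numerical harm is modest. Disagreement arises in roughly 4 to 15% of trials under the planned effect and about 2 to 5% under no effect. These figures rest on the assumed R² values, the assumed diagnosis mix, equal residual variances and 66 evaluable children.

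The more important consequences are that the trial's single confirmatory claim has no pre-stated verdict when results are discordant, and that precision may be lost if the baseline score is left out. The size of that loss depends on a baseline-to-outcome correlation that the protocol does not report.

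**What to change.** In section 2.9:

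1. Name one primary model: the 9-month summed scaled score on group, baseline summed scaled score, age stratum (<36 or ≥36 months) and diagnostic group. The group-dependent residual variance can stay.
2. State that superiority is concluded only from its group coefficient, two-sided at 0.05.
3. Label the raw model and the time-since-diagnosis model as sensitivity analyses, and say whether the latter keeps diagnosis.
4. State how children without a baseline score are handled.

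The cost is a few sentences, with no change to alpha or sample size. The mean part of the model has six coefficients (intercept, group, baseline, age and two for diagnosis), so 66 children leave 66 − 6 = 60 residual degrees of freedom. The sponsor gives up choice among models, and the missing-baseline rule must be settled. The change should be dated before any outcome data are examined by group.

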### Randomization

2.5

Following the baseline assessment, participants are randomly allocated to either intervention group (a) or intervention group (b), using centrally administered, computer-generated (REDCap) random numbers and a secure, concealed allocation procedure. The participants will be randomized in blocks with varying block sizes, which are unknown to the research team. The block size is chosen by an external researcher unaffiliated with the trial. The trial representatives, who include the children, are blinded to the randomization strategy (i.e., block size and allocation sequence). The trial representative collects demographic data upon inclusion, and after completion of the baseline assessments, the data are registered in REDCap, which generates the random group allocation. Randomization is stratified by age at inclusion (respectively, <36 and ≥36 months old) and by diagnostic group (hematologic cancers, central nervous system tumors, and extracranial solid tumors). The stratification by age is determined at 36 months to respect age-specific development and is in line with age-group divisions outlined in several guidelines (2, 14). Due to the nature of the intervention, neither the children nor the parents are blinded to their group allocation.

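### None of the three listed primary-outcome models contains baseline PDMS-3 or the age stratum, and none is named primary; the comparison stays valid but gives up precision

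*Protocol article*

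**What the plan says.** All of this is in the protocol article.

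- **Section 2.9, type of model.** The primary outcome is analysed by "analysis of covariance (ANCOVA) models with the residual variance depending on the group".
- **Section 2.9, purpose.** The models are meant to show whether group differences "could result from differences in age, diagnosis, and time since diagnosis".
- **Section 2.9, models.** The list is "1) a raw model without any adjustments, 2) a model further adjusted for diagnosis, and 3) time since diagnosis". None of the three is designated primary. PEDI is to be analysed in a similar way.
- **Section 2.9, parent knowledge test.** Only here is adjustment for baseline written out: "while adjusting for baseline scores".
- **Section 2.5.** "Randomization is stratified by age at inclusion (respectively, <36 and ≥36 months old) and by diagnostic group"; the diagnostic group has three levels. Allocation follows the baseline assessment.
- **Section 2.7 and Table 1.** PDMS-3 is scheduled at baseline and at 6, 9 and 12 months.
- **Section 2.7.1.1.** The scaled scores already take age into account.

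**The concern.** The section does not agree with itself. An ANCOVA has at least one covariate, yet the first model has none. Age is given as a reason for the modelling, yet no listed model includes it. The pre-randomization value of the outcome, normally the first covariate considered in such an analysis, is absent for PDMS-3 but explicit for the knowledge test.

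Three things are at stake:

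- **Precision.** A baseline score correlated with the 9-month score would narrow the confidence interval and correct for chance baseline imbalance, using data the trial already plans to collect.
- **Standard error.** Stratified randomization balances the strata across arms. A model that omits them does not credit that balance, so its standard error is somewhat too large.
- **Choice of result.** With three models and none primary, the headline estimate is not fixed in advance.

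**Working it through.** **Inputs.** From section 2.8: mean 20.03, SD 7.4, 25% difference, alpha 0.05, power 80%, 68 children needed, 20% missing, 82 to be recruited. From the abstract: 1:1 allocation. Two-sided testing is assumed. Two further quantities are assumptions because the article does not give them: the correlation r between baseline and 9-month scores, and the share R² of outcome variance explained by the strata. The test–retest figure of 0.94–0.98 in section 2.7.1.1 is reliability and cannot stand in for a 9-month correlation under treatment.

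**Step 1: reproduce the plan's figure.** Difference = 0.25 × 20.03 = 5.0075 points.

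n per arm = 2 × [7.4 × (1.960 + 0.842) / 5.0075]² = 34.28, or 68.6 in total. This matches the stated 68 within rounding. The sample size is therefore for an unadjusted two-group comparison with no baseline correlation.

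**Step 2: children expected at 9 months.** 82 × 0.8 = 65.6, or 32.8 per arm. The 82 equals 68 × 1.2 = 81.6 rounded up; 68 / 0.8 would be 85.

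**Step 3: power with and without baseline.** Residual SD = 7.4 × √(1 − r²). SE = SD × √(2/32.8). Power is from a two-sided t-test.

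| assumed r | residual SD | SE | 95% CI half-width (1.96 × SE) | power |
|---|---|---|---|---|
| 0 (unadjusted) | 7.40 | 1.83 | 3.58 | 77.0% |
| 0.1 | 7.36 | 1.82 | 3.56 | 77.4% |
| 0.2 | 7.25 | 1.79 | 3.51 | 78.7% |
| 0.3 | 7.06 | 1.74 | 3.42 | 80.8% |
| 0.5 | 6.41 | 1.58 | 3.10 | 87.6% |
| 0.7 | 5.28 | 1.31 | 2.56 | 96.6% |

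Power reaches 80% at r ≈ 0.27. At r = 0.5 the interval is 13% narrower (√0.75 = 0.866), which is worth 65.6 / 0.75 − 65.6 ≈ 22 further evaluable children.

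**Step 4: ignoring the strata.** If the strata explain a share R² of the variance, stratified allocation removes that share from the true variance of the difference, but the raw model's standard error still contains it. Type I error ≈ 2 × [1 − Φ(1.96 / √(1 − R²))].

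| assumed R² | type I error, raw model |
|---|---|
| 2% | 4.8% |
| 5% | 4.4% |
| 15% | 3.4% |
| 30% | 1.9% |

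A simulation of stratified block randomization (six strata, 68 children, 4,000 runs) agrees in direction and size: 3.6%, 2.9% and 2.2% at R² of 10%, 20% and 30%, against about 5% with stratum adjustment.

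**The case against.** **The wording may hide a baseline covariate.** ANCOVA implies a covariate, and describing the second model as further adjusted presupposes an earlier adjustment. A reader might infer that the plan definitely rules out baseline adjustment. The text does not support that much certainty: it is contradictory. But a raw model with no adjustments points the other way, and baseline adjustment is spelled out for the knowledge test. On either reading the section needs correcting.

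**The gain may be small.** The correlation is unknown. Sections 2.6.1 and 3.2 describe physical capacity that fluctuates from day to day under treatment, so a low 9-month correlation cannot be excluded. At r of 0.1 to 0.2 power rises by less than 2 percentage points. This stands, and it makes the size of the loss conditional.

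**The shortfall to 77% is not caused by the missing covariate.** This stands. The trial was sized for an unadjusted comparison. The shortfall comes from multiplying by 1.2 and from the normal approximation; even 34 per arm gives 78.5% by t-test. Omitting baseline does not invalidate the 68.

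**The strata point is limited.** A reader might infer that the standard errors are wrong throughout, or that false positives are inflated. Neither follows. The error is conservative, and the second model covers the diagnosis factor if diagnosis there means the three randomization groups. Because the scores are age-normed, the age stratum may explain little of the remaining variance.

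**Time since diagnosis.** A reader might infer that this covariate is nearly constant, since the 9-month visit has a ±14-day window. That window runs from treatment initiation, and the gap from diagnosis to treatment is not given, so the inference is not established.

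**Baseline scores may be incomplete.** Assessment is scheduled before allocation, but section 3.1 cites health problems, pain and unwillingness as obstacles to testing. A baseline-adjusted model therefore needs a rule for incomplete scores.

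**Conclusion.** The point holds as one of efficiency and clarity. The listed models omit the baseline PDMS-3 score and the age stratum, the list conflicts with both the ANCOVA label and the stated purpose, and no model is primary. The raw comparison remains unbiased and its type I error does not exceed 5%.

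On the article's own inputs and two-sided testing, power with about 66 evaluable children is about 77% unadjusted. With baseline adjustment it ranges from about 77% to 97% for assumed correlations of 0.1 to 0.7. The raw model's type I error lies between about 4.8% and 1.9% for an assumed 2% to 30% of variance explained by the strata, probably nearer the upper figure as far as age alone is concerned. Most of any gain would come from the baseline score. Severity: should fix.

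**What to change.** Reword section 2.9 to name one primary model: the 9-month sum of scaled scores on group, baseline sum of scaled scores, age stratum (<36 / ≥36 months) and diagnostic group (the three randomization levels), keeping the group-specific residual variance. Use the same form for PEDI, with its own baseline. Keep the raw model and the time-since-diagnosis model as sensitivity analyses.

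The cost is about 4 degrees of freedom (baseline 1, age 1, diagnostic group 2) and a simple prespecified rule, such as imputation, for any incomplete baseline score. No new data collection is needed. The change should be made before outcome data are analysed.
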